### Outcome measures

3.7

A summary of the assessment schedule is provided in Table 1 (SPIRIT).

**Table 1 tab1:** SPIRIT schedule of enrolment, interventions, and assessments (23).

Study period	Enrolment	Intervention		Postoperative period (daily: POD1-3)	Close-out
Timepoint	≤7 d pre-op	Day-1 p.m.	Day 0	POD1-3	D/C
Enrolment					
Eligibility screen	X				
Informed consent	X				
Interventions					
SGB/Sham block		X	X		
Surgery and standardized care			X		
Data collection					
Demographics, medical history	X				
MoCA	X				
ASA physical status	X				
Outcome measures					
Primary outcome					
POD incidence (3D-CAM)				X (POD1-3 bid)^a^	
Secondary outcomes					
Delirium severity (MDAS)^b^				X (POD1-3 bid)^b^	X (record)
Quality of recovery-15 (QoR-15)				X (on POD3)	
Inflammatory biomarkers (procalcitonin, CRP, IL-6, LMR, NLR)^c^	X (blood)			X (on POD1 and POD3)^c^	
Postop pain intensity (NRS)^d^				X (q8h, POD1-2)^d^	
Opioid consumption (MME)^d^				X (total, POD1-2)^d^	
Postop complications (Clavien-Dindo)^e^				X (daily)^e^	X (record)
Length of hospital stay (days)					X
Safety monitoring					
Adverse events (AEs)		X	X	X (daily)	X

a POD incidence (3D-CAM): assessed twice daily (bid) from postoperative day 1 to day 3.

b Delirium severity score: assessed daily (POD1-3). Total delirium duration is recorded at discharge (D/C).

c Inflammatory biomarkers: blood samples collected at baseline (V0), postoperative day 1, and postoperative day 3.

d Postop pain and opioid use: pain intensity (NRS) is assessed every 8 h (q8h) for the first 48 h only (POD1-2). Total opioid consumption (MME) is calculated and recorded for the first 48 h (POD1-2).

e Postop complications: monitored daily (POD1-7) and recorded at discharge.

D/C, discharge; SGB, stellate ganglion block; MoCA, Montreal Cognitive Assessment; ASA, American Society of Anesthesiologists; POD, postoperative day; 3D-CAM, 3-Minute Diagnostic Interview for CAM-defined Delirium; QoR-15, quality of recovery-15 scale; CRP, C-reactive protein; IL-6, interleukin-6; NRS, numerical rating scale; MME, morphine milligram equivalents; bid, twice daily; q8h, every 8 h.

#### Primary outcome

3.7.1

Cumulative incidence of POD from postoperative day 1 to day 3, assessed twice daily (morning 8:00–10:00, evening 18:00–20:00) using the validated 3-Minute Diagnostic Interview for CAM-defined Delirium (3D-CAM) (16). Assessors will complete standardized training (including 3D-CAM and MDAS operation, case simulation, and inter-rater reliability testing, target *κ* ≥ 0.8) before formal assessment. For sedated or intubated patients, assessment will be deferred until the patient is awake, alert, and able to cooperate; if unable to evaluate within 24 h, POD status will be recorded as missing. Delirium severity will be further evaluated using the Memorial Delirium Assessment Scale (MDAS) as described in section 3.7.1.1(4) and 3.7.2.

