#### Control of confounding variables

3.6.4

To minimize the potential impact of confounding variables on the primary outcome (POD incidence), the following measures will be implemented:

(1) Standardized perioperative management: As described in sections 3.5.1–3.5.3, all patients (both groups) will receive identical anesthesia, analgesia, and delirium prevention protocols. Any deviation from these protocols will be recorded as a protocol deviation.(2) Data collection on potential confounders: The following predefined variables, known to influence POD risk, will be collected and adjusted for in the statistical analysis: age, sex, body mass index (BMI), ASA physical status, baseline MoCA score, duration of surgery, intraoperative blood loss, intraoperative use of vasopressors, and postoperative opioid consumption (MME).(3) Statistical adjustment: In addition to the primary intention-to-treat analysis, a multivariable logistic regression model will be used to adjust for the above confounders, reporting adjusted odds ratios (aOR) with 95% confidence intervals.(4) Sensitivity analysis: A sensitivity analysis excluding patients with major protocol deviations (e.g., those who did not receive the allocated block, or those with incomplete primary outcome data) will be performed to assess the robustness of the findings.

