##### Operational details for postoperative delirium assessment

3.7.1.1

(1) Assessment team and training: Delirium assessments will be performed by two trained research assistants who are blinded to group allocation. Both assistants will undergo a standardized training program consisting of: (1) a 2-h didactic session covering the diagnostic criteria of delirium (DSM-5), the 3D-CAM, and the MDAS; (2) supervised assessments of five pilot patients (not enrolled in the trial) to achieve competency; and (3) an inter-rater reliability test, requiring a kappa coefficient ≥0.80 before starting the formal assessment. Inter-rater reliability will be rechecked every 3 months.(2) Assessment time points: The 3D-CAM and MDAS will be administered twice daily from postoperative day 1 to day 3, specifically between 8:00–10:00 a.m and 18:00–20:00 p.m. An additional assessment will be performed if a patient shows sudden changes in mental status or behavioral disturbances. At discharge, total duration of delirium (number of days with any positive 3D-CAM assessment) will be recorded.(3) Assessment for sedated or intubated patients: For patients who are sedated (RASS ≤−2) or intubated, routine 3D-CAM assessment will be deferred until the patient is awake and able to respond. In such cases, the medical record will be reviewed daily for documentation of delirium-related symptoms using the CAM-ICU (for ICU patients) or notes from the clinical team. These patients will not be excluded from the analysis; instead, the reason for missing assessment (e.g., sedation, intubation) will be recorded as a protocol deviation.(4) Delirium severity assessment: Delirium severity will be assessed using the Memorial Delirium Assessment Scale (MDAS), a 10-item, clinician-rated scale with a total score ranging from 0 to 30 (higher scores indicate more severe delirium). The MDAS will be administered twice daily from postoperative day 1 to day 3, synchronized with the 3D-CAM assessments, conducted immediately after the 3D-CAM is completed, and performed by the same trained research assistants who administer the 3D-CAM.

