#### Analysis of primary outcomes

3.9.2

The cumulative incidence of POD on postoperative days 1–3 will be compared between groups using the Chi-square test, and relative risk (RR) with a 95% confidence interval (CI) will be reported. A supplementary multivariable logistic regression will be performed to adjust for pre-specified covariates: age, baseline MoCA score, and ASA physical status. To obtain adjusted relative risk instead of odds ratio, modified Poisson regression with robust standard errors will be adopted for covariate-adjusted analysis. Multivariable logistic regression will be used only as a supplementary approach when convergence issues occur.

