#### Handling of missing data

3.9.4

Missing data will be addressed using multiple imputation by chained equations (MICE). We will generate *m* = 50 imputed datasets, including the intervention group, primary outcome, and all pre-specified covariates in the imputation model. Pooled estimates will be obtained using Rubin’s rules. Missing POD assessments are assumed to be missing at random. Longitudinal time-point information will be included in the imputation model. Complete-case analysis will be conducted as sensitivity analysis to verify the robustness of primary results.

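### The coding of delirium status in sedated or intubated patients is not reconciled between 3.7.1 and 3.7.1.1, and no planned analysis tests the missing-at-random assumption applied to them

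*Protocol article*

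**What the plan says.** The primary outcome (3.7.1) is the cumulative incidence of delirium over postoperative days 1–3 by 3D-CAM twice daily. For sedated or intubated patients the assessment is deferred, and "if unable to evaluate within 24 h, POD status will be recorded as missing".

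Section 3.7.1.1(3) covers the same patients. It also defers the 3D-CAM, but has no 24 h limit and adds that "the medical record will be reviewed daily for documentation of delirium-related symptoms using the CAM-ICU (for ICU patients) or notes from the clinical team". It continues: "These patients will not be excluded from the analysis; instead, the reason for missing assessment (e.g., sedation, intubation) will be recorded as a protocol deviation".

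Section 3.9.4 plans multiple imputation by chained equations with 50 datasets, "including the intervention group, primary outcome, and all pre-specified covariates in the imputation model", plus longitudinal time-point information. It states: "Missing POD assessments are assumed to be missing at random".

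Three planned analyses bear on missing outcomes:
- 3.9.4: complete-case analysis.
- 3.6.4: a sensitivity analysis that excludes, among others, "those with incomplete primary outcome data".
- 3.9.1: a per-protocol set that excludes patients for whom every primary outcome assessment is missing.

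The primary comparison in 3.9.2 is a chi-square test, reported with a relative risk and confidence interval.

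**The concern.** Two things are at stake. The first is the value of the binary primary endpoint for an identifiable group. A patient with a positive CAM-ICU recorded in the chart, but no completed 3D-CAM in that period, could be coded as delirious or as missing, and two analysts could each defend their choice from the text.

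The second is the assumption under which missing values are filled in. Section 3.7.1 waits until the patient is alert and cooperative, while 3.7.1.1 sets a looser condition of being awake and responsive. Section 1.1 describes delirium as a disturbance of attention, consciousness and cognition. The condition for being assessed therefore overlaps with the absence of the outcome. Missing at random would be easier to defend if the imputation model contained the reason for non-assessment. That reason is recorded under 3.7.1.1 but not named in 3.9.4. If the assumption fails, nothing planned would show it.

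**Working it through.** **1. The texts side by side**

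| Question | 3.7.1 | 3.7.1.1(3) |
|---|---|---|
| Time limit | 24 h, then missing | none |
| Other evidence | none mentioned | CAM-ICU or clinical notes, reviewed daily |
| Does that evidence set delirium status? | not stated | not stated |
| Unit of missingness | "POD status", unit not stated | the assessment |
| In the analysis? | not stated | yes, reason logged as a deviation |

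The two can be read together, but they do not yield one coding rule.

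**2. What the planned checks do.** Complete-case analysis drops patients whose outcome is missing. The 3.6.4 analysis drops those with an incomplete outcome. The per-protocol set drops only those with no assessment at all. None shifts the imputed risk, and none uses the chart or CAM-ICU result. The definitions in 3.6.4 and 3.9.1 also differ from each other.

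**3. The plan's own figure (3.8).** For 40% versus 20%, two-sided alpha 0.05 and 80% power, the unpooled formula gives (1.96 + 0.842)² × (0.4×0.6 + 0.2×0.8) / 0.2² = 78.5, against the stated 78. Then 78/0.9 = 87 per group, 174 in all. This reproduces and is not in dispute.

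**4. Size on assumed inputs.** The article gives neither the share of unassessable patients nor their delirium risk. Assume a share m of 2–10% per arm and a true risk q of 60–100%. Let assessable patients have the planned 40% and 20%. As a simplification, imputation under missing at random or complete-case analysis then returns a risk difference (RD) of 0.20 and a relative risk (RR) of 0.50. The all-randomised risk in an arm is (1 − m)p + mq. For example, with m = 5% and q = 60%: sham 0.95×0.40 + 0.05×0.60 = 0.41; SGB 0.95×0.20 + 0.05×0.60 = 0.22; RD 0.19, RR 0.54.

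| Unassessable, sham / SGB | RD | RR |
|---|---|---|
| 2% / 2% | 0.196 | 0.515–0.524 |
| 5% / 5% | 0.19 | 0.54–0.56 |
| 10% / 10% | 0.18 | 0.57–0.61 |
| 5% / 10% | 0.15–0.17 | 0.59–0.65 |
| 10% / 5% | 0.20–0.22 | 0.52 |

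The shift in the RD has no fixed direction.

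**5. Effect on the p-value.** Uncorrected chi-square, 87 randomised per arm, k unassessable per arm (assumed); counts are sham versus SGB.

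| Case | Complete case | All unassessable = POD | Only SGB unassessable = POD |
|---|---|---|---|
| k = 4, near planned effect | 33/83 v 17/83, p = 0.007 | 37/87 v 21/87, p = 0.010 | 33/87 v 21/87, p = 0.049 |
| k = 5, borderline | 30/82 v 18/82, p = 0.040 | 35/87 v 23/87, p = 0.054 | 30/87 v 23/87, p = 0.25 |

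The last column codes the unassessable sham patients as free of delirium. It is an extreme bound, not an expectation.

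**The case against.** Several points on the other side have force.

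- **The rules are compatible.** A reader might infer that the two sections contradict each other. They do not strictly do so: both defer the 3D-CAM, both treat the assessment as missing, and recording it as missing while keeping the patient fits intention-to-treat with imputation. What stands is that the role of the chart evidence is open.
- **Missing is not negative.** A reader might infer that the highest-risk patients are miscoded. An imputed value is not a coded absence of delirium, and the article gives no delirium risk for these patients.
- **A later positive counts.** Read literally, 3.7.1 could set a patient to missing after 24 h despite a positive 3D-CAM on day 2. Because the endpoint is cumulative over three days and 3.9.4 speaks of missing assessments, the natural reading is that such a patient is an observed case. One sentence would settle it.
- **The imputation model may be richer.** Section 3.9.2 names three covariates, but 3.6.4 lists nine, including surgery duration, blood loss, vasopressor use and opioid consumption. If those are meant, some markers of severity are included. Sedation, intubation and ICU status are in neither list.
- **Few patients may be affected.** Section 3.6.2 presumes extubation for all, and 3.2.2 excludes emergency surgery and severe systemic disease. Any result near 0.05 can be tipped by a few recodings, so the borderline case shows possibility, not likelihood.
- **A test can be pooled.** A reader might infer that "will be compared between groups using the Chi-square test" leaves no p-value on imputed data. The relative risk can be pooled on the log scale and combination rules for chi-square statistics exist, so this is minor.

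It would also be wrong to say that no sensitivity analysis could reveal the problem. The reason for non-assessment and the chart findings are collected, so one is feasible; none is planned. Because the article states these rules itself, their lack of reconciliation is not merely detail left to an analysis plan.

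**Conclusion.** The point holds as an unresolved coding rule for the primary endpoint, joined to a missing-at-random assumption that is doubtful for these patients and that no planned analysis relaxes. It does not show a biased result. The size depends wholly on assumed frequencies and risks. If few patients are affected, and similarly in each arm, the effect is small: an RD of 0.196 instead of 0.20 at 2% per arm, or p = 0.010 instead of 0.007 with 4 per arm. If more are affected, or unequally, the RD could range from 0.15 to 0.22 over the inputs tried, and a borderline conclusion could change. It should be settled before data accrue. Section 3.1.1 reports that nobody had been enrolled at submission.

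**What to change.** 1. Reconcile 3.7.1 and 3.7.1.1 into one coding rule. State that any positive 3D-CAM on days 1–3 makes the patient a case whatever else is missing, and that missing applies to each assessment. State whether documented CAM-ICU or chart positives count in the primary endpoint or only in a sensitivity analysis.
2. Add the recorded reason for non-assessment (sedation, intubation, ICU) to the imputation model in 3.9.4.
3. Add a delta-adjusted or tipping-point analysis by arm, including one scenario with every unassessable patient counted as delirious and one with CAM-ICU or chart positives counted.
4. Align the outcome-related exclusions in 3.6.4 and 3.9.1.
5. As a minor point, take the primary p-value from the Rubin-pooled log relative risk or risk difference.

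The chart review and the reasons are already to be collected, so the cost is wording and a little more analysis. The one real downside arises if CAM-ICU or chart positives enter the endpoint: a second source would then feed it, outside the assessors whose agreement is checked by kappa. Keeping that source to a sensitivity analysis avoids this.

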##### Operational details for postoperative delirium assessment

3.7.1.1

(1) Assessment team and training: Delirium assessments will be performed by two trained research assistants who are blinded to group allocation. Both assistants will undergo a standardized training program consisting of: (1) a 2-h didactic session covering the diagnostic criteria of delirium (DSM-5), the 3D-CAM, and the MDAS; (2) supervised assessments of five pilot patients (not enrolled in the trial) to achieve competency; and (3) an inter-rater reliability test, requiring a kappa coefficient ≥0.80 before starting the formal assessment. Inter-rater reliability will be rechecked every 3 months.(2) Assessment time points: The 3D-CAM and MDAS will be administered twice daily from postoperative day 1 to day 3, specifically between 8:00–10:00 a.m and 18:00–20:00 p.m. An additional assessment will be performed if a patient shows sudden changes in mental status or behavioral disturbances. At discharge, total duration of delirium (number of days with any positive 3D-CAM assessment) will be recorded.(3) Assessment for sedated or intubated patients: For patients who are sedated (RASS ≤−2) or intubated, routine 3D-CAM assessment will be deferred until the patient is awake and able to respond. In such cases, the medical record will be reviewed daily for documentation of delirium-related symptoms using the CAM-ICU (for ICU patients) or notes from the clinical team. These patients will not be excluded from the analysis; instead, the reason for missing assessment (e.g., sedation, intubation) will be recorded as a protocol deviation.(4) Delirium severity assessment: Delirium severity will be assessed using the Memorial Delirium Assessment Scale (MDAS), a 10-item, clinician-rated scale with a total score ranging from 0 to 30 (higher scores indicate more severe delirium). The MDAS will be administered twice daily from postoperative day 1 to day 3, synchronized with the 3D-CAM assessments, conducted immediately after the 3D-CAM is completed, and performed by the same trained research assistants who administer the 3D-CAM.

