#### Secondary outcomes

3.7.2

(1) Delirium severity, assessed using the Memorial Delirium Assessment Scale (MDAS), and total delirium duration (number of days with a positive 3D-CAM assessment).(2) Quality of recovery- 15 (QoR-15) score on postoperative day 3.(3) Plasma levels of inflammatory biomarkers (procalcitonin, C-reactive protein, interleukin-6, lymphocyte-to-monocyte ratio [LMR], neutrophil-to-lymphocyte ratio [NLR]) at baseline, postoperative day 1, and postoperative day 3.(4) Postoperative pain intensity (NRS) trajectories and total opioid consumption (morphine milligram equivalents) over 48 h.(5) Incidence of postoperative complications (Clavien-Dindo classification) and length of hospital stay.

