### Sample size calculation

3.8

Based on prior literature reporting POD incidences ranging from 35 to 48% (2–4), we adopted a best-case scenario assumption for sample size planning: a baseline incidence of 40% in the sham group and a 50% relative risk reduction (to 20%) in the SGB group. Under these assumptions (*α* = 0.05, power = 80%, two-sided Chi-square test), 78 patients per group are required. Accounting for an estimated 10% dropout rate, the final sample size is 174 participants (87 per group).

We acknowledge that this effect size may be optimistic, especially given that our protocol excludes patients with preexisting cognitive impairment and includes a multicomponent delirium prevention bundle. If the true effect is smaller, this study may be underpowered for the primary outcome. Therefore, the results should be interpreted as hypothesis-generating, and future meta-analyses will be needed to confirm smaller effects.

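### Total delirium duration is tallied at discharge from 3D-CAM-positive days, but scheduled 3D-CAM stops on postoperative day 3, so the trial cannot support a claim about total duration

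*Protocol article*

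**What the plan says.** Section 3.7.2, item (1), lists as a secondary outcome "total delirium duration (number of days with a positive 3D-CAM assessment"), with no time window. Section 3.7.1.1, item (2), repeats the definition and adds when it is noted: "At discharge, total duration of delirium (number of days with any positive 3D-CAM assessment) will be recorded". Footnote b of Table 1 agrees: "Total delirium duration is recorded at discharge (D/C").

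The instrument that supplies the positive days has a fixed schedule. Section 3.7.1.1, item (2), says "The 3D-CAM and MDAS will be administered twice daily from postoperative day 1 to day 3". Footnote a of Table 1 says it is "assessed twice daily (bid) from postoperative day 1 to day 3", and the discharge cell of the 3D-CAM row is empty. Section 3.7.1 gives the same window for the primary outcome.

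One further route to a positive assessment exists, in the same item of 3.7.1.1: "An additional assessment will be performed if a patient shows sudden changes in mental status or behavioral disturbances". Neither its instrument nor its last day is given.

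**The concern.** The definition, instrument, schedule and recording time of this outcome are all fixed in the protocol, and they do not fit together. The name and the recording time suggest follow-up to discharge, while the schedule ends on day 3. A patient whose delirium starts on day 3 can contribute at most one scheduled positive day, however long the episode lasts.

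At stake is what the report may say. Delirium duration is among the secondary objectives in section 2.2. With the plan followed as written, a between-group difference would be presented as an effect on total duration, although part of each longer episode was never assessed. The window applies equally to both groups, but the number of days lost depends on the day of onset. The recorded count therefore mixes duration with onset time. Unscheduled assessments after day 3, if they happen, would make the count depend on staff noticing a change and on length of stay, which is itself a secondary outcome.

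**Working it through.** The protocol states no figure for delirium duration, so there is none to reproduce. The structural check uses only the schedule; the size check uses assumptions, labelled as such.

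**1. What the schedule can count.** Inputs: scheduled window, days 1 to 3 (section 3.7.1.1 and Table 1); outcome, number of days with a positive 3D-CAM (3.7.1.1 and 3.7.2). For an episode of length L days starting on day s ≤ 3, days counted = min(L, 4 − s). For s > 3 the count is 0.

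| True length | Onset day 1 | Day 2 | Day 3 | Day 4 |
|---|---|---|---|---|
| 1 day | 1 | 1 | 1 | 0 |
| 2 days | 2 | 2 | 1 | 0 |
| 3 days or more | 3 | 2 | 1 | 0 |

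The only possible values are 0, 1, 2 and 3. The same 3-day episode is recorded as 3, 2, 1 or 0 days depending on when it starts. This part needs no assumption.

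**2. How much could be cut off (illustration).** Assumed: geometric length with mean 1.5, 2 or 3 days, so the daily probability of continuing is q = 1 − 1/mean; onset on days 1/2/3 in 60/30/10%, 40/40/20% or 20/50/30% of cases. An episode starting on day s is still running after day 3 with probability q^(4 − s).

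- Mean 3 days, q = 2/3: the probabilities for onset on days 1, 2 and 3 are 0.296, 0.444 and 0.667. With 60/30/10: 0.178 + 0.133 + 0.067 = 0.38. With 20/50/30: 0.059 + 0.222 + 0.200 = 0.48.
- Mean 2 days: 0.20 to 0.30 over the three splits.
- Mean 1.5 days: 0.09 to 0.16.

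The recorded mean for onset on day s is (1 − q^(4 − s))/(1 − q). For a true mean of 3 days this gives 2.11, 1.67 and 1.00 for onset on days 1, 2 and 3. The overall recorded mean is 0.6 × 2.11 + 0.3 × 1.67 + 0.1 × 1.00 = 1.87 with the early split, and 0.2 × 2.11 + 0.5 × 1.67 + 0.3 × 1.00 = 1.56 with the late split.

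**3. What a pure shift in onset would do (illustration).** Assume that half of the day-1 cases move to day 2 and half of the day-2 cases to day 3, so 40/40/20 becomes 20/40/40, with true lengths unchanged.

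| True mean (days) | Recorded, 40/40/20 | Recorded, 20/40/40 | Fall |
|---|---|---|---|
| 1.5 | 1.31 | 1.22 | 7% |
| 2 | 1.50 | 1.35 | 10% |
| 3 | 1.71 | 1.49 | 13% |

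A shift lowers the count only when the moved episode then runs past day 3 or starts after it. A 1-day episode moved from day 1 to day 2 still counts 1.

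**The case against.** The best defence is that recording at discharge does not mean observing until discharge. Footnote e of Table 1 has complications monitored on days 1 to 7 and recorded at discharge, so the table elsewhere tallies an earlier fixed window at close-out. Footnotes a and b, read together, can give a day 1 to 3 count in the same way. That reading is plausible. It does not rescue the outcome, because the quantity is then not a total duration and the window is nowhere stated for it. Other outcomes do carry a window: incidence over three days, pain and opioids over 48 hours, complications over days 1 to 7. An analysis plan could add the window, but it could not recover assessments that were never scheduled.

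Second, the consequence is limited. This is part of one secondary outcome, the secondary outcomes are under false discovery rate control, and the authors call the findings exploratory. The primary outcome has the same window but declares it openly. This stands.

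Three stronger readings are tempting, and the documents do not support them:

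- A reader might infer that the outcome is strictly capped at 3 days. That is certain only for scheduled assessments; a triggered assessment after day 3 is not ruled out.
- A reader might infer that the block will look beneficial merely by delaying delirium. Nothing in the protocol suggests that it delays onset; the stated hypothesis is lower incidence and severity. Step 3 shows that the count is sensitive to onset, not that such an artefact will occur.
- A reader might take the percentages as estimates for this trial. Every input to them is assumed.

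**Conclusion.** The point holds as a mismatch between an outcome's name and definition and the schedule that feeds it. From scheduled 3D-CAM the outcome takes only the values 0 to 3 and is cut off for episodes continuing past day 3. Triggered assessments leave it unclear whether later days can enter, and if they do, they enter selectively. A claim about total delirium duration therefore cannot be supported. This conclusion rests on the protocol text alone.

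The size of the loss cannot be obtained from the documents. The 9% to 48% of episodes still running at the end of day 3, and the 7% to 13% fall under delayed onset, depend on assumed geometric lengths, assumed onset splits and, for the latter, an assumed delay. The primary outcome is not affected. Whether duration is compared in all randomised patients, with 0 for no delirium, or only in delirious patients is a separate choice and no part of this point.

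**What to change.** Choose one of two, and amend sections 3.7.1.1 and 3.7.2 and Table 1 to match.

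(a) Redefine the outcome as delirium days within postoperative days 1 to 3, counting scheduled assessments only. State that it is cut off at day 3 and that a lower count may reflect later onset. Renaming does not remove the dependence on onset day, so this sentence is needed. The cost is wording and a narrower claim.

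(b) To keep a claim about duration, have the same blinded research assistants continue the 3D-CAM in patients still positive at the last day-3 assessment, until negative or discharge. State that onset after day 3 is not captured. The cost is a few extra short assessments in a minority of patients.

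Section 3.1.1 reports that no participant had been enrolled at submission. If that is still so, either change can apply to every participant; assessments not made cannot be recovered later.
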